### Intervention

#### Control Group

Participants randomized to the control group will receive usual care (ie, physician visits every 3-6 months and therapy according to respective treatment guidelines) and a CAir Desk for 12 weeks. The CAir Desk will assess daily symptom burden, physical activity, and spirometry data. Patients will receive daily COPD assessment questionnaires through the smartphone and will be required to wear the physical activity monitor during the day and night. The threshold for sufficient physical activity and spirometry data requires measurements on at least 3 days per week. In contrast to the intervention group, participants will not receive any feedback or scores of the telemonitoring efforts, such as the daily reported COPD assessment test and daily physical activity, nor will they receive any virtual coaching.

In case of any worsening symptoms, no alert message will be generated. Patients will have to contact their general physician or pulmonologist individually and independently. No modification of any treatment will be made by the study team during the study.

#### Intervention Group

Participants randomized to the intervention group will receive a CAir Desk and a hybrid digital coaching intervention for 12 weeks.

The first week will serve to measure baseline levels of daily physical activity. Starting in the second week of the study, participants will receive individualized feedback on their daily physical activity through the CAir chatbot app. We calibrated the daily target step count to be 15% above the patient's baseline value. The telemonitoring solution will send alerts to the study team in case the patient’s daily COPD assessment test score drops by 2 or more points in 2 consecutive days. A 2-point drop is considered the minimum clinically relevant difference [16]. In those cases, a physician will contact patients by phone to discuss if any further actions have to be taken to treat or prevent a possible exacerbation (ie, taking medication or planning a physician visit).

In addition, the CAir chatbot will provide virtual coaching to the patients of the intervention group: (1) a self-paced educational component about living with COPD based on the *Living well with COPD* program [9] that aims to foster patient empowerment through engagement and awareness and (2) a dynamic motivational interviewing component to increase physical activity, one of the most critical behaviours that are of prognostic relevance. The chatbot is rule-based with predefined answer options only and does not have any anthropomorphic visual cues. We used IBM Watson as a development tool. Data gathered via the CAir Desk autonomously feeds into the chatbot interaction without time lag as a digital trigger, that is, the script of the chatbot automatically adapts if the patient has not achieved the required target step count.

During 2 time periods of the intervention, a COPD expert will grant optional additional support via chat, making the entire intervention a hybrid solution (involving the chatbot and human health care provider), which has been described in other studies [17].

The overall study is depicted in Figure 3.

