**Figure 2 figure2:**
[figure not shown]
CAir data management architecture and data flow.

Further, a CAir chatbot backend was implemented using IBM cloud functions and the IBM Watson Assistant for just-in-time interactions with the patients through a chatbot frontend provided by docdok.health. Timed triggers initiate daily conversations, such as informative sessions, physical exercises, or patient feedback through the docdok app. Further, these functions scan the databases for daily activities, degrading scores of the COPD assessment test, or nonadherence to the study protocol, notifying the study team through the docdok dashboard for health care professionals to intervene. The content and logic of the chatbot conversations are implemented using the IBM Watson Assistant, which is queried by the cloud functions to manage the conversation flow between the patient docdok app and the backend.

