The COPD Assessment Test [23], a validated patient-completed questionnaire, will be provided daily on the smartphone to capture the gradual change in symptom burden.

Changes in spirometry will be measured daily with the forced expiratory volume in 1 second and forced vital capacity. Lung function testing will be performed according to the guidelines of the European Respiratory Association and the American Thoracic Society [24].

Total change in daily physical activity will be expressed as the number of steps per day. This will be assessed using a physical activity tracker. The device will be worn as a wrist band. Wearing times will be throughout day and night. During times of lower activity (eg, while having dinner, reading, or watching TV), the device may be placed on the CAir Desk, recharging its battery and synchronizing the data.

The number of recorded coughs per night will be used as a proxy for the total change in nightly cough. Compliance with the COPD medication will be captured daily and compared within and between the intervention and control group.

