**Secondary outcome**						
	Symptom burden	COPD^a^ assessment test		✓	Daily	✓
	Spirometry	Forced expiratory volume in one second		✓	Daily	✓
		Forced vital capacity		✓	Daily	✓
	Functional exercise capacity	1-minute sit-to-stand test		✓		✓
		6-minute walk test		✓		✓
	Compliance with COPD^a^ medication	Self-reported			Daily	
	Physical activity	Step count			Daily	
	Cough	Night-time cough count			Daily	

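### The intervention-arm alert is printed as a fall in the COPD Assessment Test score, which is the wrong sign if a higher score means more symptom burden

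*Protocol article*

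**What the plan says.** The Intervention Group section gives the only numeric alert rule in the article. The study team is alerted when the daily COPD Assessment Test "score drops by 2 or more points in 2 consecutive days". The next sentence justifies the size of the threshold and repeats the direction: "A 2-point drop is considered the minimum clinically relevant difference", citing reference 16. A physician then phones the patient to decide whether anything needs to be done "to treat or prevent a possible exacerbation".

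Two other places describe the same alert:

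- Technological Study Setup (text after Figure 2) says that backend functions scan for, among other things, "degrading scores of the COPD assessment test, or nonadherence to the study protocol", and notify the study team.
- Control Group states what controls do not get: "In case of any worsening symptoms, no alert message will be generated".

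The article names what the test measures in three places:

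- Control Group: "The CAir Desk will assess daily symptom burden, physical activity, and spirometry data", followed by the statement that patients receive the daily questionnaire.
- Secondary Outcomes: the test "will be provided daily on the smartphone to capture the gradual change in symptom burden".
- Table 1: the test is the assessment listed for "Symptom burden".

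Nowhere does the article say whether a higher or a lower score on this test is worse.

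**The concern.** An alert meant to catch deterioration is written as a fall in a score that the article treats as a measure of burden. A falling burden score would ordinarily mean fewer symptoms. The word for a fall appears in two adjacent sentences, once in the rule and once in its justification, so it is hard to dismiss as a single slip.

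The rule names a score, a size and a time window, so a programmer, a study nurse or a team replicating the intervention could apply it exactly as printed. The resulting phone call is a safety-relevant part of the intervention, and controls do not receive it. With the sign reversed, a sustained rise in burden would trigger no call, while patients who are getting better would be phoned. What is at stake is clinical follow-up in the intervention arm and whether the intervention delivered is the one intended.

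**Working it through.** There is no figure in the plan to reproduce. The check concerns sign only.

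**Inputs**

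- Printed trigger (Intervention Group): change in score ≤ −2, over 2 consecutive days.
- Purpose of the alert (Technological Study Setup, Control Group, Intervention Group): worsening of symptoms.
- Construct measured (Control Group, Secondary Outcomes, Table 1): symptom burden.
- Scoring direction: not stated. Both possibilities are therefore carried through.

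**Formula**

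Let d be the change in score. Let s = +1 if a higher score means more burden and s = −1 if a lower score means more burden. The change in burden is s × d. An alert that serves its stated purpose needs s × d ≥ +2.

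**Results**

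| Scoring direction | Worsening by 2 or more means | Printed trigger | Printed trigger detects |
|---|---|---|---|
| Higher = more burden (s = +1) | d ≥ +2 | d ≤ −2 | improvement |
| Lower = more burden (s = −1) | d ≤ −2 | d ≤ −2 | worsening |

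For example, with invented scores and s = +1, a move from 14 to 16 gives d = 16 − 14 = +2. That is worsening, and the printed rule stays silent. A move from 20 to 18 gives d = 18 − 20 = −2. That is improvement, and it meets the printed 2-point fall.

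The exact meaning of the 2-day window does not matter here. Whether it means a fall on each of two days, a fall across two days, or two days below a reference value, the sign requirement is the same.

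**Which row applies**

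The table cannot settle this; only the text can. Three places label the score as burden, which favours the first row. The only text favouring the second row is the disputed pair of sentences, and using them to settle the direction would be circular. The Hypotheses section gives a direction for the SGRQ, where a decrease goes with an effective intervention. That is a different instrument and does not fix the direction here. It does show that a reader of this article cannot assume that a falling questionnaire score means worsening.

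**The case against.** The strongest reply is that the decisive premise is not in the article. A burden label names a construct, not its numeric coding, and the cited sources that would settle the coding are not at hand. Leaving the scoring key of an instrument to its reference would be normal in a condensed article. This part stands: the finding is conditional on an inferred direction. It is still not a complaint about omission, because the article prints an explicit rule that, on the ordinary reading, works against its own stated purpose.

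A second reply is that the intent is clear. Three places say that the alert is for deterioration, so a reader would take the word loosely. That may well be what the authors meant, but a rule with a number and a window invites literal use.

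A third reply is that the software was already built when the article was written, and Technological Study Setup describes it as scanning for deteriorating scores. The same section also gives the study team dashboard access to daily summaries. This stands as well. A reader might infer that the running system is inverted and that worsening patients are being missed. The article does not support that: nothing in it shows that the code follows the printed sentence, and the backend description suggests otherwise. Dashboard access is a partial safeguard but not an alert.

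Finally, a 2-point fall might be exactly what reference 16 reports. In that case the threshold sentence would be a correct citation even though the trigger is wrong. This cannot be checked here, so that sentence is for the authors to verify.

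**Conclusion.** The point holds in conditional form. If a higher COPD Assessment Test score means more burden, which the burden label implies but the article never states, the printed trigger is the reverse of what the alert is for. If a lower score means more burden, the printed trigger is right, but nothing outside the disputed sentences points that way. Confidence is medium, because the direction is inferred.

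The size cannot be expressed as a count. The article gives no score distribution or alert rate, so no frequency of missed or unnecessary calls can be derived. A reader might also infer that the trial's main comparison is compromised. The article does not support that: the primary outcome is the change in SGRQ from baseline to week 12, and the method of its analysis does not use the alert rule. The consequence is confined to clinical follow-up and fidelity in the intervention arm, and to anyone who reproduces the intervention from the article. It should be fixed, since the correction is trivial and an inverted alert would defeat its stated purpose.

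**What to change.** 1. In Intervention Group, reword the trigger so that the alert is sent when the score worsens by 2 or more points in 2 consecutive days. State the direction in which the score worsens (an increase, if higher means more burden).
2. Have the authors check the following sentence on the 2-point threshold against reference 16, and change its wording only if that source does not support a fall specifically.
3. Confirm once that the deployed alert fires on worsening scores.

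The 2-point size and the 2-day window stay as they are. The cost is one reworded clause, a statement of direction, one look at a source and one check of the code. No extra patients, visits or analyses are needed.

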**Figure 3 figure3:**
[figure not shown]
CAir Study overview.

### Outcomes

#### Primary Outcome

As a primary outcome, we will measure the delta in HRQOL, which we will assess with the SGRQ [12] from baseline to week 12 (the end of the intervention). The SGRQ is a well-established self-administered questionnaire that is valid, reliable, and responsive for the population affected by COPD. Participants will not have access to their completed questionnaires and scoring to reduce potential bias.

#### Secondary Outcomes

To evaluate the effectiveness of CAir holistically, we will include a set of secondary endpoints. Changes in the functional exercise capacity will be analyzed using the 1-minute sit-to-stand test and the 6-minute walk test, which have been demonstrated to be reliable, valid, and responsive in assessing functional exercise capacity in patients with COPD [18,19].

The 1-minute sit-to-stand test is performed using a standardized protocol [18,20]. A conventional chair without armrest and a seat height of 46 cm will be used. The patient will be instructed to stand up and sit down as often as possible at a self-chosen speed over 1 minute. The number of sit-stand repetitions will be counted by the assessor. Verbal encouragement will not be provided during the test, but the patient will be told after 45 seconds that another 15 seconds are left until the test is over. Patients will be allowed to stop at any time during the test. When standing up, the patient’s legs have to be completely straight, and when sitting down, the bottom has to have clear contact with the chair. The patients will be told to place their hands at the hips and will not be allowed to use their hands or arms to assist movement. Measurements of heart rate, peripheral capillary oxygen saturation, and modified Borg scale of perceived exertion [21] will be performed before and after the 1-minute sit-to-stand test using the same assessment tools as for the 6-minute walk test.

The 6-minute walk test will be performed according to technical standards of the American Thoracic Society/European Respiratory Society [22]. The test will be carried out on a marked circular 75-m hallway and patients will be told to walk as far as possible within the 6 minutes. The walking distance (in meters) will be registered at the end of the test. Patients will be allowed to take breaks during the test if necessary; time recording, however, will not be interrupted. Standardized instructions and phrases of encouragement will be given each minute. Oxygen supplementation will be installed if required, and the patients will carry their oxygen device during the test. Before and after the test, heart rate and oxygen saturation will be measured with a pulse oximeter (Masimo Rad-5v, Masimo Corp) connected to the index finger. Ratings of perceived exertion and dyspnea will be evaluated using a 0-10 modified Borg scale.

The COPD Assessment Test [23], a validated patient-completed questionnaire, will be provided daily on the smartphone to capture the gradual change in symptom burden.

Changes in spirometry will be measured daily with the forced expiratory volume in 1 second and forced vital capacity. Lung function testing will be performed according to the guidelines of the European Respiratory Association and the American Thoracic Society [24].

Total change in daily physical activity will be expressed as the number of steps per day. This will be assessed using a physical activity tracker. The device will be worn as a wrist band. Wearing times will be throughout day and night. During times of lower activity (eg, while having dinner, reading, or watching TV), the device may be placed on the CAir Desk, recharging its battery and synchronizing the data.

The number of recorded coughs per night will be used as a proxy for the total change in nightly cough. Compliance with the COPD medication will be captured daily and compared within and between the intervention and control group.

#### Exploratory Endpoints

Exploratory endpoints to support the analysis will also be considered. We will investigate the usability and limitations of CAir through specifically designed questionnaires (eg, usability questionnaire) and structured focus group interviews at the end of the study. In the case of an exacerbation, we will compare the data assessed by CAir before and after the event. We will also analyze air quality by continuously measuring volatile organic compounds, which are harmful organic chemicals found in products such as cleaners and in cigarette smoke. Serious adverse events related to the intervention, such as medical occurrences that require in-patient hospitalization or prolongation of existing hospitalization, will be captured as safety endpoint variables.

A detailed overview of primary, secondary, and exploratory endpoints, including their measurement frequency, is depicted in Table 1.

**Table 1 table1:** Overview of the information collected during screening, at baseline, during the intervention and at the end of the study.

Outcome		Assessment	Cadence			
			Screening	Baseline visit	Within the intervention	End of study visit

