## Introduction

### Background

Chronic obstructive pulmonary disease (COPD) is a chronic lung disease commonly caused by exposure to noxious particles (primarily from smoking) and characterized by respiratory symptoms (ie, dyspnea, cough, and sputum) and airflow obstruction [1]. Patients experience persistent respiratory symptoms with periods of acute worsening (exacerbations) and a substantial decrease in health-related quality of life (HRQOL). In 2016, about 251 million people worldwide were affected by COPD [2]*.* COPD is projected to become the third-leading global cause of death by 2030 [3]. In addition to the health implications, COPD causes a substantial economic burden on the individual and the health care systems [4]. There is no cure for COPD. However, effective treatment such as medication, smoking cessation, and physical exercise helps to relieve symptoms and prevent exacerbations [5]. Active disease management to reduce the burden of COPD and improve HRQOL therefore plays a crucial role in the therapeutic strategy.

Effective COPD management plans follow a patient-centered approach and aim to (1) prevent disease progression through the reduction of risk factors, (2) improve exercise tolerance, (3) improve health status, and (4) relieve symptoms [5]. Best practice treatment of COPD should be multidimensional and include medical care, self-management strategies, physical activity coaching, and behavioral change approaches [6-8]. One of these evidence-based disease management programs is *Living well with COPD* [9,10]. The program was developed by a Canadian consortium and is based on a disease self-management approach that covers educational topics as well as lifestyle coaching and physical activity advice supervised by health care professionals [9]. A randomized clinical trial showed that compared to usual care in a multicenter setup, the *Living well with COPD* intervention program reduced hospital admissions due to COPD exacerbations, emergency department visits, and unscheduled physician visits and improved HRQOL significantly [9]. A recent clinical trial conducted in Switzerland confirmed these results [8]. The implementation of the program, however, is both time and cost intensive.

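### The safety endpoint admits serious adverse events only if related to the intervention, so the arms qualify by different routes and an unbiased safety comparison is not secured

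*Protocol article*

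**What the plan says.** Under Exploratory Endpoints, the article states that "Serious adverse events related to the intervention, such as medical occurrences that require in-patient hospitalization or prolongation of existing hospitalization" are to be captured as safety endpoint variables. No other safety variable is named. Table 1, which is offered as the overview of the primary, secondary and exploratory endpoints, has no row for serious adverse events.

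The same section deals with exacerbations separately: "In the case of an exacerbation, we will compare the data assessed by CAir before and after the event". That is a before-and-after look at sensor and symptom data around an event, not a count of events by arm.

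Exposure differs between the arms as follows.

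- Control Group: this arm has usual care plus the Desk over the same 12 weeks. These patients get no feedback or scores, "nor will they receive any virtual coaching". For deterioration, the text says "In case of any worsening symptoms, no alert message will be generated".
- Intervention Group: "Participants randomized to the intervention group will receive a CAir Desk and a hybrid digital coaching intervention for 12 weeks". This arm also has a step target with individual feedback, alerts to the study team with a physician's call, and optional expert chat.

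The article does not say who judges relatedness or how, or whether the word intervention includes the Desk.

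**The concern.** A safety endpoint that is to be compared between arms needs the same admission rule in each arm. A rule based on relatedness to the intervention cannot be the same when one arm receives less of the intervention than the other. Any difference in counts then mixes a true difference in event rates with a difference in what is eligible to be counted.

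The events at risk of being left out are informative ones. The alert pathway is there to help treat or prevent exacerbations, and the Background section cites the parent programme as having "reduced hospital admissions due to COPD exacerbations, emergency department visits, and unscheduled physician visits", together with improved quality of life. A hospitalisation for an ordinary exacerbation is the event through which benefit or harm of such a pathway might show, and it is also one that may be judged unrelated. The endpoint could then read zero in both arms although patients had been hospitalised.

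**Working it through.** No figure in the article bears on this point: it states no serious-event rate and no power for safety. The check is mainly a comparison of the texts, with a small calculation for scale.

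**Step 1: which events enter the endpoint.** Each serious event is classed by its judged cause and set against the stated definition. The narrow reading takes the intervention to be the coaching package (feedback, coaching, alerts). The wide reading adds the CAir Desk and its measurements.

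| Judged cause | Intervention arm | Control arm, narrow reading | Control arm, wide reading |
|---|---|---|---|
| Coaching, feedback, step target or alert call | enters | cannot occur | cannot occur |
| Desk or its measurements | enters on the wide reading only | does not enter | enters |
| Unrelated, such as an ordinary exacerbation | does not enter | does not enter | does not enter |

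On the narrow reading the control count is 0 whatever the true hospitalisation rate. On the wide reading it can exceed 0, but controls still have one route to qualify where the intervention arm has two. The third row is excluded on either reading.

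**Step 2: which reading the text supports.** The Intervention Group wording lists the Desk and the coaching intervention as two things, which favours the narrow reading. The heading Intervention covers both arms, and Strengths and Limitations describes the intervention as technology-heavy, which favours the wide one. The text does not settle it.

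**Step 3: how many events are at stake.** Inputs: 28 intervention and 14 control patients (Sample Size) and 12 weeks per patient (Methods). The 12-week risk p of at least one serious event is not in the document. It is assumed here over a range and taken as equal in both arms. Expected patients with an event = n × p. Chance of none in an arm = (1 − p)^n.

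| Assumed p | Expected of 28 | Expected of 14 | Expected of 42 | Chance of none among 14 controls |
|---|---|---|---|---|
| 2% | 0.56 | 0.28 | 0.84 | 0.98^14 = 75% |
| 5% | 1.4 | 0.7 | 2.1 | 0.95^14 = 49% |
| 10% | 2.8 | 1.4 | 4.2 | 0.90^14 = 23% |
| 15% | 4.2 | 2.1 | 6.3 | 0.85^14 = 10% |

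These are counts with all serious events included. Under the stated definition, only the part judged related would enter.

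**Step 4: what full capture could show.** Power of a two-sided Fisher exact test at 0.05 is the sum of the binomial probabilities of all tables with p ≤ 0.05. With 28 against 14 patients (intervention against control), it is about 5% for risks of 20% against 10%, 23% for 30% against 10%, and 27% for 5% against 20%. If no control patient had an event, the one-sided 95% upper limit for the control risk would still be 1 − 0.05^(1/14) = 19%. Full capture gives a fair description, not a test.

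**The case against.** The strongest reply is that this article condenses a fuller protocol that is not shown, and that collection, causality assessment and reporting of serious events are commonly left to that document. The sentence says that related events will be captured. It does not say that others go unrecorded, and it does not confine capture to one arm. This stands as a limit on the point: a reader might infer that only related events are recorded and that most hospitalisations would be lost, and the article does not say so. It does not remove the point, because the definition of the endpoint is stated rather than left out, and it is the stated definition that treats the arms differently.

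A reader might also infer that the control arm has no events by construction, so that no comparison is possible. The text does not support this as a general statement. Controls have the Desk for 12 weeks, with daily questionnaires, spirometry and a wearable, in a section whose heading covers both arms. A Desk-related event could be counted there. The zero count follows only on the narrow reading.

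Two further inferences should be avoided. The article does not say that relatedness is judged by staff who know the arm; its assessor blinding is not extended to causality review either way. It also does not rank hospital admissions above the other benefits it lists for the parent programme.

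Finally, safety sits among the exploratory endpoints of a 42-patient quality-of-life trial, and Step 4 shows that full capture would not yield a powered comparison. That is correct. It limits what the data can show, but it is no reason to apply unequal admission rules to the few events that occur.

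**Conclusion.** The point holds in this form: the safety endpoint as defined makes relatedness a condition of entry, gives the arms different routes to qualify on either reading of the intervention, and leaves out hospitalisations judged unrelated in both. It therefore does not secure an unbiased comparison of safety between arms.

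The size is modest. Under an assumed 12-week risk of 5% to 15%, equal in both arms, 2.1 to 6.3 of 42 patients would have a serious event; at 2% it would be fewer than one. What share would be judged related is unknown. The conclusion does not touch the primary analysis, and it would lapse if the full protocol already defines the endpoint as all serious events in both arms. It is a worthwhile improvement at low cost, not a flaw that threatens the trial.

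**What to change.** Replace the sentence under Exploratory Endpoints with a definition that does the following:

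- counts all serious adverse events, including every hospitalisation and every death, in both arms from randomisation to week 12, whatever the judged cause;
- records relatedness as a separate attribute of each event;
- states whether the intervention includes the CAir Desk, so that the attribute has one meaning in both arms;
- reports the number of events and of patients with at least one event by arm, descriptively and without a powered test.

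Add a matching row to Table 1. If the full protocol already provides for this, the article need only be brought into line with it.

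The cost is a few more case-report forms for 42 patients over 12 weeks and slightly more analysis work. No visits are added and the primary endpoint is unchanged. The change is best made while data are being collected, since events not recorded at the time may be hard to recover later.
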